## Abstract

**Background:**

Depression is a debilitating mental health problem that tends to run a chronic, recurrent course. Even when effectively treated, relapse and recurrence rates remain high. Accordingly, interventions need to focus not only on symptom reduction, but also on reducing the risk of relapse by targeting depression-related disturbances that persist into remission. We are addressing this need by investigating the efficacy, acceptability and feasibility of a MEmory Specificity Training (MEST) programme, which directly targets an enduring cognitive marker of depression - reduced autobiographical memory specificity. Promising pilot data suggest that training memory specificity ameliorates this disturbance and reduces depressive symptoms. A larger, controlled trial is now needed to examine the efficacy of MEST. This trial compares MEST to an education and support (ES) group, with an embedded mechanism study.

**Methods/Design:**

In a single blind, parallel cluster randomised controlled trial, 60 depressed individuals meeting diagnostic criteria for a current major depressive episode will be recruited from the community and clinical services. Using a block randomisation procedure, groups of 5 to 8 participants will receive five weekly sessions of MEST (n = 30) or education and support (n = 30). Participants will be assessed immediately post-treatment, and at 3- and 6-months post-treatment (MEST group only for 6-month follow-up). Depressive symptoms at 3-month follow-up will be the primary outcome. Secondary outcomes will be change in depressive status and memory specificity at post-treatment and 3-months. The 6-month follow-up of the MEST group will allow us to examine whether treatment gains are maintained. An explanatory question will examine variables mediating improvement in depression symptoms post-treatment and at 3-month follow-up.

**Discussion:**

This trial will allow us to investigate the efficacy of MEST, whether treatment gains are maintained, and the mechanisms of change. Evidence will be gathered regarding whether this treatment is feasible and acceptable as a low-intensity intervention. If efficacy can be demonstrated, the results will support MEST as a treatment for depression and provide the foundation for a definitive trial.

**Trial registration:**

NCT01882452 (ClinicalTrials.gov), registered on 18 June 2013.

## Background

Depression is a pervasive mental health condition that is a leading cause of disability worldwide
[1]. As well as causing significant distress to the individual and their families, the burden of disease at the societal level is estimated to cost the United Kingdom approximately £9 billion each year
[2]. Epidemiological studies have established depression as a lifelong chronic illness, with more than 80% of individuals experiencing repeated episodes
[3]. Of concern is that with each successive depressive episode experienced, there is increased risk of future recurrence
[4]. Gold standard psychological treatments, such as Cognitive Behavioural Therapy (CBT), can successfully treat depressive illness. However, only about half of patients receiving treatment will respond, and, even if they do, the risk of relapse and recurrence remains high
[3]. If depressive disorders are to be more effectively treated in the future, a better understanding of factors that increase the risk of relapse/recurrence is needed. One way to address this need is to focus on cognitive markers of depression that do not necessarily remit following treatment.

It is widely accepted that depression is characterised by a range of disturbances in autobiographical memory. Specifically, the tendency to recall overgeneral memories (that is, memories of broader, more general categories of events rather than memories of a particular discrete instance) has been identified as a stable cognitive marker of depression
[5]. Depressed individuals have difficulty retrieving specific memories of past autobiographical events in response to cue words. For example, in response to the cue word ‘excited’ there is a tendency to provide summarised categories of similar events (for example, *birthday parties*) or details of an event that occurred over a protracted time period (for example, *my holiday to Wales*), rather than a specific event (for example, *going to the Leonard Cohen concert in London last month*)*.*

Research over the past two decades has established that such overgeneral memory recall is reliably associated with depressive symptoms in both clinical and analogue samples. Furthermore, overgeneral memory recall is not just a product of being depressed - following the recovery of a depressive episode, reduced specificity remains stable. That is, formerly depressed patients show comparable levels of generality to their depressed counterparts (for example,
[6,7]), suggesting that it is a trait vulnerability factor for future recurrence. In support, longitudinal findings show that the tendency to recall overgeneral memories predicts the course of depression prospectively (for example,
[8-11]). Furthermore, overgeneral memory recall is associated with negative psychological outcomes that exacerbate depression including impaired problem solving ability
[12], difficulty in imagining future events
[13], heightened rumination
[14] and executive dysfunction
[15]. Therefore, this relative imbalance in the specificity of recalled autobiographical events is a key driver of depressive illness.

Theoretical accounts originally conceptualised overgenerality as a mode of memory retrieval that develops in an attempt to minimise the potential for negative emotion experience that arises from the recall of specific distressing memories
[14]. This avoidance conceptualisation has since been elaborated upon, with proponents of the CaR-FA-X model (that is, capture and rumination, functional avoidance, impaired executive control) suggesting that a number of processes, either alone or in combination, account for the tendency to retrieve overgeneral memories among depressed individuals. Specifically, Williams and colleagues
[5] suggest that three mechanisms underlie overgeneral memory: capture and rumination, functional avoidance and impaired executive control (for recent review, see
[16]). A comprehensive analysis of this model is beyond the scope of this protocol, but in short, the capture and rumination mechanism relates to the possibility that overgeneral memory is facilitated by mnemonic information, which activates ruminative processes during memory retrieval. In support, studies have found that experimentally induced ruminative processing leads to overgeneral memory recall while non-ruminative thinking does not
[17-20]. The second factor, functional avoidance, is similar to the initial conceptualisation of overgeneral memory as an avoidance mechanism, whereby remembering autobiographical events overgenerally has been suggested to reduce the affective impact of emotional memories. Consistent with this proposal are findings showing that avoiding specific recall immediately following an aversive experience reduces emotional distress
[21]. Third, the model asserts that impaired executive control limits the ability of an individual to remain focused on retrieving a specific memory. To support this, numerous studies have found that overgeneral memory recall is associated with impaired executive control on a range of outcomes including verbal, spatial, and memory measures
[15]. While empirical evidence is consistent with the three processes identified in the model, on-going research in the area is needed to more fully elucidate the mechanisms and interactions underlying overgeneral memory recall.

From a clinical perspective, the reliable and robust relationship between overgenerality and adverse psychological phenomena make reduced memory specificity an attractive target for therapeutic change. Moreover, research suggests that overgeneral memory recall is not a fixed feature of an individual’s mnemonic style
[22] and can be modified
[23]. As derived from the existing framework, it follows that enhancing access to specific memories should yield therapeutic benefit. This elegantly simple premise was first empirically addressed by [name], Williams and Hermans
[24], who developed a brief MEmory-Specificity Training (MEST) procedure. The programme was designed as a four-session, group training program whereby participants simply practiced recalling specific events repeatedly in response to different cue words. In this pilot study of 10 depressed female inpatients, results showed that memory specificity improved following the training, along with improvements in symptoms and depression-related processes (for example, rumination, problem-solving and cognitive avoidance). While promising, this first pilot included a small sample size, no control condition, and no follow-up.

Having established that in principle, memory specificity can be trained using this programme, it was followed up with a randomised clinical trial comparing MEST to a non-active control condition in a group of bereaved, depressed Afghani teenage refugees living in Iran
[25]. Consistent with the earlier pilot study
[24], training improved specificity levels in the MEST group. Symptom measures at post-training indicated that there was no group difference in depressive symptoms. However, participants who received MEST had significantly lower symptom levels than those in the control group at 2-month follow-up, and they were no longer in the clinical range. Finally, this improvement in depression in the MEST group was mediated by improvements in memory specificity from the beginning to the end of training.

The data from these two studies are encouraging - they suggest that MEST may improve outcomes in depression, once shifts in memory specificity have had time to gain traction in day-to-day cognitive processing. Similar encouraging data are also emerging from the post-traumatic stress disorder (PTSD) literature
[26]. It is now time for the next stage of the treatment development process. Medical Research Council (MRC) guidelines
[27] for the development of complex interventions specify that once the necessary pre-clinical and pilot research foundations have been completed, a Phase II exploratory trial to evaluate the efficacy, feasibility and acceptability of an intervention is needed. We are addressing this need by conducting a randomised controlled clinical trial in which MEST is compared to an appropriate, active control group.

If MEST is established as efficacious, acceptable to patients, and feasible to deliver, it would confer a number of advantages. First, it is a relatively brief and thus cost-effective intervention that may be suitable as an adjunct to more comprehensive therapies or as a standalone, low-intensity intervention for mild forms of depression. Moreover, it can be delivered by individuals with limited training and experience, and, as it does not involve addressing emotional difficulties, lends itself to implementation in challenging clinical contexts by individuals who do not necessary have the training in how to manage sensitive issues that arise in clinical groups. This is particularly important in countries with fewer mental-health resources
[28]. From a public health perspective, this treatment is very much in line with UK government initiatives aiming to deliver more accessible, cost-effective psychosocial interventions, such as the Improving Access to Psychological Therapies (IAPT) programme
[29]. Another advantage associated with MEST is that it targets a cognitive marker of depression that does not necessarily improve as an individual comes out of a depressive episode (for example,
[8,30]). This provides reason to expect that this intervention may reduce future relapse and recurrence via its impact on specificity-related processes.

A key question that remains unanswered is exactly *how* MEST works. It is hypothesised that MEST training changes processes believed to mediate the impact of the mode of memory retrieval on depression, namely, by decreasing cognitive avoidance, reducing rumination, improving problem solving, and improving executive control. However, the degree to which changes in these variables is mediated by changes in memory specificity is unknown. An embedded mechanism study will allow investigation of the processes mediating change.

In summary, there is promising evidence suggesting that MEST offers a novel way through which a key memory disturbance linked to depression and adverse psychological sequelae may be targeted. In this cluster RCT we will compare MEST to an active education and support (ES) intervention control condition in a sample of depressed British adults. This trial was designed to answer four key questions. First, does MEST improve specificity and reduce depression? Second, are gains maintained over the longer term? Third, is MEST superior to an education and support intervention in its effects on depression and specificity? Fourth, what are the mechanisms mediating any treatment effects?

## Methods/Design

### Study design

The design is a single-blind, parallel cluster RCT comparing MEST to an ES intervention, with an embedded mechanism study. The intervention duration is equivalent in both conditions and participants will be assessed four times - at baseline, at post-treatment, and at 3-month and 6-month follow-up time points. The first three assessment points (that is, baseline, post, and 3-month follow-up) are face-to-face and include the full battery of assessment measures, including primary and secondary outcomes and process measures. Assessment at 6 months will be for the MEST group only and will take place via phone. This final assessment includes primary and secondary outcomes only (with the exception of the Autobiographical Memory Test; AMT).

### Participants and recruitment

A total of sixty individuals aged 18 to 65 with a principle diagnosis of major depressive disorder (recurrent episode) will be randomised to either MEST (*n* = 30) or ES (*n* = 30). Inclusion criteria are a diagnosis of major depressive disorder (recurrent) according to the DSM-V; a diagnosis of a current major depressive episode; the presence of moderate symptoms defined as a Beck Depression Inventory (BDI-II)
[31] score of >13, and memory specificity of less than 0.70, as assessed on the AMT
[32]. Participants need to have a baseline level of specificity of less than 0.70 to be invited into the trial because a higher level illustrates that memory specificity is not a difficulty for that individual, and there will be minimal opportunity for specificity-related benefits to accrue. Participants continue with their usual treatment (for example, antidepressant medication or psychological therapy) during the trial. Exclusion criteria are: high levels of suicidality or harm to others (assessed via interview and exclusion according to clinical judgement), a secondary diagnosis of another affective disorder or a psychotic disorder; current drug/alcohol abuse or dependence all assessed via the Structured Clinical Interview for the Diagnostics and Statistics Manual – SCID-V,
[33]; a diagnosed Axis II disorder (assessed via participant report); and the presence of head trauma or organic brain damage (assessed via participant report).

There are three pathways through which participants will be recruited. The first is directly from the community via posters and advertisements around the Cambridge (UK) area. The second is from our departmental volunteer panel comprising individuals with a history of depression who have previously participated in our research. The third will be via clinical services offered within the Cambridgeshire and Peterborough Foundation Trust. Patients in these services will be identified by members of the clinical team and provided information about the trial. They will be able to opt in by contacting us directly.

Participants who have previously been assessed by our research team will be notified about the study by email. Participants who have not previously volunteered in our research (that is, community members and patients in clinical services) who express interest will be provided written information about the study (via email or post) after contacting us. After reading the study information sheet, interested participants will be administered a brief phone screen (using items from the Mood Module of the SCID-IV) to verify whether they meet criteria for a current major depressive episode. Those who do will then be invited to attend a session at the Medical Research Council Cognition and Brian Sciences Unit for a full baseline assessment involving clinical interviews and experimental tasks, as outlined below.

### Participant allocation

Eligible participants will be cluster randomised using a blocked randomisation procedure with 5 to 8 participants in a group to receive the intervention. This will be achieved using computer-generated, quasi-random numbers and will be conducted by the trial statistician ([name]), blind to study objectives. Once generated, this information is passed to the trial lead ([name]), who informs the project coordinator responsible for delivering the intervention ([name]) within 48-hours of the commencement of a given group.Figure 
1 summarises the trial CONSORT (consolidated standards for reporting trials) diagram. Following randomisation, patients are offered treatment for five consecutive weeks (commencing within four weeks of the baseline assessment).

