#### Treatment integrity

Two clinical psychologists with experience in treating adult depression will deliver the MEST and ES interventions. Treatment fidelity and clinician adherence will be established using continued monitoring and through independent rating. After every session, clinicians will complete the Treatment Fidelity Checklist, which is a session-by-session measure of compliance with the protocol, and these will be evaluated during weekly clinical supervision with the trial lead. In addition, a random 25% of the audio-taped treatment sessions will be rated for adherence to the manuals by an experienced clinician, independent of the core trial team. Homework completion will be monitored and assessed using self-report questionnaire measures.

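### The group allocation goes to the trial lead when it is generated, not when the therapy group is closed, which leaves an avoidable gap in concealment

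*Protocol article*

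**What the plan says.** All of the procedure stands in the protocol article, mostly under Participant allocation.

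- Unit: eligible people are "cluster randomised using a blocked randomisation procedure with 5 to 8 participants in a group to receive the intervention". Under Participants and recruitment, the sixty participants "will be randomised to either MEST (*n* = 30) or ES (*n* = 30").
- Generation: the randomisation "will be conducted by the trial statistician", who is described as unaware of the study's aims.
- Hand-over: "Once generated, this information is passed to the trial lead", "who informs the project coordinator responsible for delivering the intervention" "within 48-hours of the commencement of a given group".
- Timing for participants: treatment follows randomisation, "commencing within four weeks of the baseline assessment".

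Two other sections bear on who holds the information. Under Treatment integrity, the therapists complete fidelity checklists and "these will be evaluated during weekly clinical supervision with the trial lead", so the lead is part of the working team. Under Blinding, the masking provision covers the outcome raters; participants and therapists know the arm.

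**The concern.** The 48-hour rule shows that the authors wanted the arm hidden until a group is about to begin. It binds only the last person in the chain. The person one step earlier receives the allocation as soon as it exists, and no stated safeguard links that moment to a closed membership list.

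This matters because the clusters are not existing units such as clinics. They are assembled from individuals who arrive by three recruitment routes, the group size may vary from 5 to 8, and up to four weeks may pass between a person's baseline and the start of treatment. Whether someone joins this group or the next is therefore partly a scheduling decision, and one exclusion criterion rests on clinical judgement. If anyone who can influence those decisions knows or can guess the arm, the arms may differ in who enters them. Blinded raters do not repair that, particularly as the primary outcome is self-reported BDI-II. Baseline covariates adjust only for what was measured.

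**Working it through.** The article gives no number of groups and no block size, so there is no figure of its own to reproduce on this point. Its one derived number, 24 per arm after 20% attrition, is right (30 × 0.80 = 24) and has no bearing here.

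**Step 1: number of groups.** Inputs: 30 per arm (Participants and recruitment) and groups of 5 to 8 (Participant allocation).

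- Fewest per arm: 30 / 8 = 3.75, rounded up to 4.
- Most per arm: 30 / 5 = 6.
- Both arms: 2 × 4 = 8 to 2 × 6 = 12 groups.

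**Step 2: who can know the arm, and when.** The text allows two readings.

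- *Sequence generated ahead of recruitment.* The lead holds the arms of groups that are not yet filled. The coordinator does not learn a group's arm until about its start.
- *Each arm generated after its group is filled.* The lead learns the arm when membership can no longer change, and the list gives no foreknowledge.

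The section places eligibility before randomisation in general terms, and it speaks of telling the coordinator about one group at a time. Neither statement says that a group is full and fixed when its arm is generated, so the article does not decide between the readings.

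**Step 3: what past allocations reveal without the list.** Those delivering treatment know the past arms, because therapists are not blinded and the same two psychologists deliver both interventions. Assume balanced permuted blocks of 2k groups with the block size known or guessed. A place is fully determined when all places left in the block belong to one arm. The expected number of such places per block is

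E = Σ (j = 1 to k) of 2 × C(2k − j, k) / C(2k, k)

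- Blocks of 2 (k = 1): 2 × 1/2 = 1; share 1/2 = 50%.
- Blocks of 4 (k = 2): 2 × 3/6 + 2 × 1/6 = 1 + 0.333 = 1.333; share 1.333/4 = 33%.
- Blocks of 6 (k = 3): 2 × 10/20 + 2 × 4/20 + 2 × 1/20 = 1 + 0.4 + 0.1 = 1.5; share 1.5/6 = 25%.

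With 12 groups, which all three block sizes divide evenly, that is on average 6, 4 or 3 groups whose arm could be deduced beforehand.

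**The case against.** The strongest reply is that the article never says a full list is drawn up in advance. Its wording also fits generation group by group after people are eligible and assessed, in which case the lead knows an arm only briefly and too late to matter. The recruitment text gives the lead no part in screening, baseline assessment or placement, and the supervision role concerns treatment after allocation. The coordinator is kept unaware until about group start, the raters are blind, and the four-week limit restricts how long anyone could be held back for a preferred group. A journal article may also leave list closure and release logs to the full protocol, and the CONSORT figure, which might show the order of steps, is not visible.

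Much of this stands. A reader might infer that the lead holds every forthcoming allocation from the outset, or that the lead uses it in choosing or placing participants. The documents support neither. Nor do they support a bias of any size in BDI-II points: such a figure would need an invented number of displaced participants and an invented severity for each. The predictability shares rest on assumed block sizes, and the article does not make clear how its blocks relate to its groups.

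The reply does not remove the point. The routing through the lead is a stated procedure and not a silence. It sends the allocation to a member of the core team on generation, when it could go straight from the statistician to the coordinator after closure.

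**Conclusion.** The point holds as an avoidable risk to allocation concealment, not as demonstrated bias. The stated chain protects the coordinator and leaves the lead unprotected. Foreknowledge from the list depends on one fact that the article does not give: whether an arm is generated before its group is filled. If it is always generated after membership is fixed, that part of the concern falls away. The small number of groups, 8 to 12, follows from the article's own figures. The 50%, 33% and 25% depend on assumed balanced blocks of 2, 4 or 6 and on someone knowing or guessing the block size. No effect on the treatment estimate can be quantified from the documents, and the sample size is unaffected.

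**What to change.** Change the hand-over. The statistician keeps the sequence and releases one group's arm at a time, directly to the coordinator, only after that group's membership list is closed and all its baseline assessments are complete. The times of closure and release are logged. The present timing close to group start can remain.

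This removes foreknowledge through the list. Some chance of guessing from past arms remains with so few groups; the article discloses no block size, so nothing in it needs correcting on that account.

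The cost is about one message per group, 8 to 12 in all, with no change to the sample size or the interventions. Recruitment began in January 2014, so the change would protect groups not yet formed. If practice already works this way, a sentence in Participant allocation saying so is enough.
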